### Assessments

An equally weighted domain composite score of executive functions will constitute the primary outcome of the present study. The other cognitive domain (visuo-cognition, attention and working memory, memory, language) equally weighted composite scores, an equally weighted global cognition composite score based on the equally weighted domain composite scores, single test scores, as well as the assessments of non-motor symptoms, (fine) motor abilities, quality of life, and the feasibility of the intervention constitute the secondary outcomes. Physical activity measured by accelerometry, brain imaging parameters, and polysomnography parameters constitute exploratory outcomes.

#### Neuropsychology and motor assessments

All subjects will undergo clinical and neuropsychological assessments, including paper–pencil cognitive and motor evaluations. The in-person assessments take around 2.5 h to complete, including a short break according to the participant’s needs. The test battery will be administered by psychologists or graduate students of Psychology or Medicine at all time points. The outcome assessors will be thoroughly trained in administering and scoring the assessments. Following the in-person assessments, participants digitally fill out questionnaires on various non-motor symptoms, quality of life, and lifestyle activities, which are sent to them via SoSci Survey (SoSci Survey GmbH, Munich, Germany). An automatic reminder email is sent to the participants, if they do not complete the questionnaire within 1 week of their study visit. A complete list of all cognitive assessments, motor evaluations, and questionnaires, including references, is presented in Table 1. Parallel test forms are used if available (i.e., alternating between time points). Test scores are standardized into *z*-scores, percentage ranks (PR), or *T*-scores using published normative data, as available. All evaluations are double-checked and digitalized using the four-eye principle. All standardized scores are transformed into *z*-scores during data preprocessing to create the domain composite scores. Table 1 provides an overview of the assignment of cognitive tests to the respective domains.

**Table 1 Tab1:** Neuropsychological and motor assessments in CogTrAiL-RBD

Domain	Abbreviation	Assessment	Reference	Baseline	Posttest I and II	Follow-up I and II

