## Methods/design

### Study design and setting

The study CogTrAiL-RBD is designed as a monocentric, single-blinded, delayed-start randomized controlled trial with two study arms aiming to consecutively recruit 80 individuals with iRBD confirmed by polysomnography from the continuously expanding local iRBD cohort at the University Hospital Cologne in Germany [54]. Participants will be randomly assigned to either the early intervention group or a delayed-start control group. Forty participants will be randomly assigned to each group (parallel group phase, superiority). The delayed-start control group will receive the same intervention after a 6-month waiting period, with the early intervention group undergoing the intervention for a second time to separate symptomatic from potentially disease-modifying effects (open-label phase, exploratory) [55].

Figure A-1 presents the schematic trial design and Appendix Figure A-1 further illustrates the timeline for participants. At baseline assessment (t0, week 0), the study will be explained to the participants. Subsequently, the participants will provide written informed consent and answer to a demographic interview. All participants with iRBD will undergo comprehensive clinical and neuropsychological assessments at the t0 visit and 6 weeks post allocation (posttest I, t1, week 6). A follow-up assessment (follow-up I, t2, week 33) will be conducted after 6 months. Subsequently, the second intervention phase for both the early intervention group and the delayed-start control group begins, followed by another clinical and neuropsychological assessment (posttest II, t3, week 39). Finally, a follow-up assessment (follow-up II, t4, week 66) will take place after an additional 6 months.

There are three optional study modules for individuals with iRBD that accompany the mandatory clinical and neuropsychological assessments: (i) the MRI module consisting of structural and functional MRI at each assessment time point; (ii) the accelerometry module consisting of physical activity tracking with accelerometers at each assessment time point; and (iii) the polysomnography module including two polysomnographies, one before the start of the intervention and one within the last 2 weeks of the intervention. Additionally, an age- and sex-matched HC group will be examined at the first assessment time point, participating in the comprehensive clinical and neuropsychological assessments, the MRI module and the accelerometry module.

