### Randomization and blinding

Randomization in CogTrAiL-RBD is based on a minimization procedure designed to minimize differences between the early intervention group and the delayed-start control group in age, sex, and premorbid IQ [63]. The minimization randomization is implemented using the R package *Minirand* [64]. We aim at a 1:1 ratio of the number of subjects in the early intervention group and the delayed-start control group. The covariates age, sex, and premorbid IQ will be equally weighted (1/3 each). The participants with iRBD will be consecutively randomized following the clinical and neuropsychological t0 baseline assessment by a person not involved in t1 to t4 data collection, preferably by their individual contact person, who will assign the participants to the intervention and monitor their training progress.

The assessments will be double-blinded at t0 baseline (i.e., randomization will be carried out after the t0 baseline assessment) and single-blinded at t1 to t4 posttests and follow-ups (i.e., outcome assessors do not know the participant’s group allocation). Any violations of blinding will be documented, e.g., if participants do not fully comply with the explicit instruction not to give any clues about their experimental group allocation to the outcome assessors.

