#### Computerized multi-domain cognitive training

The computerized training will be delivered by the CE-certified class-I medical device “HeadApp/NEUROvitalis Digital” (HelferApp GmbH, https://start-headapp.helferservices.net) offering adaptive, multi-domain cognitive training accessible from home with internet access. Participants will train for a total of 15 training sessions across 5 weeks, 40 min per day, three times a week resulting in a total training duration of 600 min, which is comparable to previously published interventions [34]. The training consists of six different tasks addressing one primary cognitive domain each: executive functions, working memory, episodic memory, attention, visuo-cognition, and language. The training starts with the lowest difficulty and adapts to training performance concerning higher difficulty and task complexity levels. With higher difficulty levels, all tasks involve a strong executive component, leading to a strong executive focus of the applied cognitive training. The training tasks are based on the scientifically validated NEUROvitalis program (ProLog, Therapie und Lernmittel GmbH, Cologne) [65–69]. Depending on their group assignment, participants receive their login credentials and information about the training during their t0 or t2 visit. The training will be monitored weekly on the HeadApp/NEUROvitalis Digital website by the individual’s contact person, and any queries of participants will be answered by telephone or email, depending on the participant’s choice.

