#### Accelerometry: physical activity tracking

All willing participants will be asked to wear a wrist-mounted movement sensor measuring linear acceleration and angular velocity on their dominant hand for 7 days around each assessment time point. The sensors will be distributed either during the assessment session (along with a prepaid return envelope) or sent to the participants 10 days prior the next assessment. The participants will be instructed to wear the sensor as much as possible throughout their days and nights. Additionally, participants will be asked to fill out a diary noting their bedtimes, daily activities, and periods when they are not wearing the device.

The CE-certified movement sensor used in this study is the AX6 from Axivity Ltd, Newcastle upon Tyne, England. Detailed information about the AX6 and the wrist strap can be found in the Data Sheet documents available on the Axivity website (https://axivity.com/product/ax6). The sensors will be configured to record data continuously for 7 consecutive days and nights (168 h) at a sampling rate of 100 Hz with an accelerometer range of ± 8 g. Sensor set-up and data storage will be managed using the open source AX3/AX6 OMGUI Configuration and Analysis Tool (https://github.com/digitalinteraction/openmovement/wiki/AX3-GUI). Data retrieval from the sensor is only possible via a USB cable connection. Data will be saved in the Continuous Wave Accelerometer (*.cwa) binary format containing the raw actigraphy data, metadata, and device configurations.

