#### Magnetic resonance imaging

Extensive brain imaging with a 3 T SIEMENS PRISMA scanner equipped with a 64-channel head coil will be conducted at the Research Center Jülich near Cologne for all willing participants at all time points (t0–t4). The MRI scanning will preferably occur within 7 days of the clinical and neuropsychological assessment. However, in case of technical difficulties with the scanner or timing issues with the participants (e.g., illness or personal reasons), it may be conducted up to 3 weeks apart. During MRI measurements, at least one member of the study team is present. This person will be supported either by another member of the study team or by a medical-technical radiology assistant of the Research Center Jülich. The net scanning time for all sequences lasts 69:33 min. The sequences, their features and specifications, spatial resolution, repetition times (TR), and echo times (TE) as the basic pulse sequence parameters are described in Table 2. The MRI data will be exported and saved in the DICOM format (*.dcm).

**Table 2 Tab2:** Magnetic resonance imaging protocol CogTrAiL-RBD

Sequence	Features	Duration
T1-weighted	The T1-weighted sequence will be used to monitor cortical thickness, gray matter volume, and deformation. These metrics are well-established markers which might change upon training. Sequence parameters: 0.9 mm isotropic MP2RAGE, TR 2500.0 ms, TE 2.22 ms	6:24 min
Neuromelanin-sensitive turbo spin echo	Turbo spin-echo (TSE) sequences allow for contrast evaluation of neuromelanin containing structures, i.e., locus coeruleus and substantia nigra. Measures of locus coeruleus integrity like volume, voxels with highest intensity as well as contrasts of spatial subdivisions will be performed [111]. Such measures will elucidate the role of an intact locus coeruleus as prerequisite for successful cognitive training. Sequence parameters: 0.4 × 0.4 × 1.8 mm^3^ resolution, TR 825.0 ms, TE 18.00 ms	7 × 2:24 min = 16:48 min

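### The t0 self-report questionnaires are not assured to precede allocation, so the baseline of nine repeated self-report instruments can be unblinded and post-randomization

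*Protocol article*

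**What the plan says.** All of the following is from the protocol article.

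- **Randomization.** Under Randomization and blinding: "The participants with iRBD will be consecutively randomized following the clinical and neuropsychological t0 baseline assessment". The same section calls the t0 assessments double-blinded, on the ground that "randomization will be carried out after the t0 baseline assessment". It does not define what the t0 baseline assessment includes.
- **Handover.** Under Computerized multi-domain cognitive training: "Depending on their group assignment, participants receive their login credentials and information about the training during their t0 or t2 visit". Healthy lifestyle information places the booklet at the same visit.
- **Questionnaires.** Under Neuropsychology and motor assessments: "Following the in-person assessments, participants digitally fill out questionnaires on various non-motor symptoms, quality of life, and lifestyle activities". They are sent through an online survey tool. A reminder follows if they are not completed within a week of the visit, and no closing date is given.
- **Accelerometry.** Seven days of wear around each time point. "The sensors will be distributed either during the assessment session", or they are mailed 10 days ahead of the next assessment.
- **MRI.** Preferably within 7 days of the assessment. In case of scanner or scheduling problems, "it may be conducted up to 3 weeks apart". Before or after is not stated.
- **Consent.** Under Study design and setting: "At baseline assessment (t0, week 0), the study will be explained to the participants"; written consent follows at that visit.
- **Polysomnography.** The first recording must precede the start of training. No such rule is given for the other t0 measurements.
- **Analysis.** t0 is one of three response times in the mixed model. The reported effect is the between-group difference in mean change, divided by the pooled baseline standard deviation.

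**The concern.** A baseline is useful because allocation cannot have influenced it. Here the early group leaves the t0 visit knowing its allocation, with training access and a booklet that encourages more activity and a Mediterranean diet. It can answer the t0 questionnaires afterwards. The delayed group receives nothing until t2. A difference between arms at t0 could then be caused by allocation, and the change from t0 would carry that difference with the opposite sign.

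This touches declared outcomes. Non-motor symptoms and quality of life are secondary outcomes, and seven of the nine repeated questionnaires stand in the non-motor block of Table 1. IPAQ stands under motor and PDSS under sleep. LAQ, IPAQ and MEDAS measure the behaviours that the booklet promotes, so they are the most exposed.

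**Working it through.** **1. Sample size, to see whether it is touched.** Inputs from Sample size and power calculation: d = 0.5, two-sided alpha 0.05, power 80%, correlation 0.8, dropout 5%.
- The two-sample t-test gives 63.8, so 64 per group, as stated.
- 64 × √(1 − 0.8²) = 64 × 0.6 = 38.4, which the article takes as 38 per group, N = 76.
- 76 / 0.95 = 80, as stated.

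The figure reproduces. It rests on the executive composite, which comes from in-person tests done before randomization, so the timing problem does not alter it.

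**2. Order of events at t0 for the early group.**
- In-person assessment, then randomization (Randomization and blinding).
- Credentials and booklet during the t0 visit (the two intervention sections), so allocation is known by then.
- Questionnaires after the in-person tests, with the reminder counted from the visit (Neuropsychology and motor assessments).

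Study design and setting agrees: t0 is week 0, and t1 is both week 6 and six weeks after allocation, so allocation falls in week 0. Nothing requires the questionnaires to be submitted before the handover.

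**3. Which measures are exposed.** The article does not itemise the online battery. I assume it contains the self-report scales that Table 1 repeats at baseline, posttest and follow-up: BDI-II, FSMCF, SF-36, PSQ, NMSQ, LAQ, MEDAS, IPAQ and PDSS, nine in all. The cognitive tests, MDS-UPDRS-III, Timed Up and Go and Purdue Pegboard are in-person and not exposed.

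**4. How a shifted baseline enters the effect.** Let δ1 be the true standardised effect at t1 and δ0 any shift at t0 caused by allocation. The interaction estimates δ1 − δ0. For illustration, assume δ1 = 0.5 and 38 per arm, and let a share f of the effect already be present at t0, so that the change difference is 0.5 × (1 − f). Power is a normal approximation with standard deviation of change √(2(1 − ρ)):

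| f | Change difference | Power, ρ = 0.8 | Power, ρ = 0.5 |
|---|---|---|---|
| 0 | 0.50 | 0.93 | 0.59 |
| 0.10 | 0.45 | 0.87 | 0.50 |
| 0.25 | 0.375 | 0.73 | 0.37 |
| 0.50 | 0.25 | 0.41 | 0.19 |

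The article gives d = 0.5 and ρ = 0.8 for executive functions only. Their use for questionnaires, the value ρ = 0.5 and every f above zero are my assumptions. f may be near zero. A shift in the opposite direction would inflate the estimate: δ0 = −0.05 gives 0.5 + 0.05 = 0.55.

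**5. MRI timing.** Training is 3 sessions a week for 5 weeks, 15 in all. With t1 six weeks after allocation, the slack is 6 − 5 = 1 week. If the scan follows the visit:
- 7 days after t0: 0 sessions if training starts after the slack week, 1 × 3 = 3 if it starts at once; 0 to 20% of 15.
- 21 days after t0: 2 × 3 = 6 or 3 × 3 = 9 sessions; 40 to 60% of 15.

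**The case against.** The strongest reply is that the article condenses a fuller protocol, that randomization is said to follow the t0 baseline assessment, and that Table 1 marks the questionnaires as baseline measures. The intended order may therefore be questionnaires first. That is arguable, but it does not fit the other statements: credentials are handed out during the visit, while the reminder is timed from the visit and so presupposes completion after it. The order is stated, not merely left out.

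A second reply is that participants know their group at every later self-report anyway, because the control is passive. That is true and cannot be avoided at t1 and t2, but it can be avoided at t0.

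Several stronger readings are tempting and are not supported:
- **That the t0 MRI and sensor data are collected after allocation.** Consent at the visit makes this likely, but neither window has a direction and one sensor route precedes an assessment.
- **That a t0 scan typically falls after 9 of 15 sessions.** This needs both the exceptional 3-week limit and training that starts at the visit. The preferred window is 7 days.
- **That the sensor week lies in the first training week.** Receiving credentials is not starting, and there is about a week of slack. For early-group participants in the polysomnography module, a recording must come between t0 and the first session.
- **That the bias runs toward no effect.** Neither its size nor its direction can be derived from the article.

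MRI and accelerometry are also exploratory, with separate analysis plans to be preregistered.

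**Conclusion.** The point holds for the questionnaires. As written, nine repeated self-report instruments can have an unblinded, post-allocation baseline, and the double-blind description of t0 is assured only for the in-person tests. The bias in the time-by-group effect is of unknown size and may be negligible. It is most plausible for LAQ, IPAQ and MEDAS. This rests on the stated sequence and on the assumption that these nine scales form the online battery.

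For MRI and accelerometry the supported conclusion is weaker: the protocol does not ensure that the t0 measurement precedes allocation or training. A reader might infer that the whole baseline, or the main result, is compromised. It is not: the primary composite, the other in-person cognitive tests and the in-person motor tests are all taken before randomization.

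**What to change.** **Participants still to be enrolled.** Run the minimization and release allocation, credentials and booklet only after the t0 questionnaires are submitted, either at the visit or within a few days of it. Trial status reports 55 of 80 enrolled on 10 May 2024, so at most 25 remained then, and recruitment was expected to end in June 2024. The cost is a longer visit (the in-person part already takes about 2.5 hours) or a delay of a few days. Since t1 is counted from allocation, a delay slightly lengthens the t0–t1 interval of the primary outcome, in both arms alike. For that reason I would not hold allocation for up to 3 weeks to wait for a scan. Instead, schedule the t0 scan and, where feasible, the sensor week before the first training session, as is already required for the first polysomnography.

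**Participants already enrolled.** Flag each t0 questionnaire, sensor and MRI record by its date relative to allocation and to first training login. Add a sensitivity analysis that does not use the later records as baseline. This needs no new assessments if those dates are on file, and the analysis is not due until the last t2 visit. It cannot restore a clean baseline, but it shows how many records are affected and whether the results depend on them.

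**Text.** Limit the blinding statement under Randomization and blinding to the in-person tests, and state the t0 order explicitly.

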**Cognition**						
Cognitive reserve	LEQ	Lifetime of Experiences Questionnaire	Valenzuela and Sachdev [76]; Roeske et al. [77]	X		
Cognitive testing				X	X	X
**Overall cognitive state**						
Subjective cognition	Multi-SubCoDE	Multiple Domain Subjective Cognitive Decline Evaluation	Not published yet, available upon request from the corresponding author			
Global cognition	MoCA	Montreal Cognitive Assessment: Version B or A	Nasreddine et al. [56]			
Social cognition	RMET	Reading the Mind in the Eyes Test	Baron‐Cohen et al. [78], Kynast et al. [79]			
**Executive**						
Semantic fluency	RWT sem	Regensburger Wortflüssigkeitstest: Food or Animals	Aschenbrenner et al. [80]			
Phonemic fluency	RWT phon	Regensburger Wortflüssigkeitstest: P- or S-words	Aschenbrenner et al. [80]			
Set-shifting	TMTB/A	Trail Making Test (TMT): TMT-B/TMT-A	Reitan [81]; Aebi [82]			
Inhibition	Stroop-I	Stroop Interference	Bäumler and Stroop [83]			
Logical reasoning	LPS-4	Leistungsprüfsystem 50 + : Subtest 4, Fluid Reasoning, Version A or B	Sturm et al. [84]			
**Visuo-cognition**						
Construction	ROCFT	Rey Osterrieth Complex Figure Test (ROCFT): Figure Copy	Rey [85], Strauss et al. [86]			
Perception	LPS-11	Leistungsprüfsystem 50 + : Subtest 11, Visual Perception, Version A or B	Sturm et al. [84]			
Spatial perception	BJLO	Benton Judgment of Line Orientation, Version V or H	Benton et al. [87], Benton [88]			
	LPS-7	Leistungsprüfsystem 50 + : Subtest 7, Spatial Rotation, Version A or B	Sturm et al. [84]			
**Attention and working memory**						
Working memory	DSback	Wechsler Adult Intelligence Scale (WAIS): Digit Span backwards	Wechsler [89]			
	BTA	Brief Test of Attention	Schretlen [90]			
Processing speed	TMT-A	Trail Making Test A	Reitan [81]; Aebi [82]			
Attention	Stroop-W	Stroop Word	Bäumler and Stroop [83]			
	Stroop-C	Stroop Color	Bäumler and Stroop [83]			
**Memory**						
Verbal memory	DSforw	Wechsler Adult Intelligence Scale (WAIS): Digit Span forwards	Wechsler [89]			
	VLMT-Learn	Verbaler Lern- und Merkfähigkeitstest (VLMT): Wordlist Learning, Version C or A	Helmstaedter and Durwen [91]			
	VLMT-Rec	Verbaler Lern- und Merkfähigkeitstest (VLMT): Wordlist Recall, Version C or A	Helmstaedter and Durwen [91]			
Visuo-spatial memory	ROCFT	Rey Osterrieth Complex Figure Test (ROCFT): Figure Recall	Rey [85], Strauss et al. [86]			
**Language**						
Naming	ACL-Naming	Aphasia Check List, Subtest Naming	Kalbe et al. [92]			
Semantic and abstraction	WAIS	Wechsler Adult Intelligence Scale (WAIS): Similarities	von Aster and Neubauer [93]			
**Non-motor**						
Depressive symptoms	BDI-II	Beck Depression Inventory (BDI-II)	Beck et al. [94]	X	X	X
Fatigue	FSMCF	Fatigue Scale for Motor and Cognitive Functions	Penner et al. [95]	X	X	X
Quality of life	SF-36	Short Form Health 36 (SF-36 V2.0)	Ware et al. [96]; Bullinger [97]	X	X	X
Perception of stress	PSQ	Perceived Stress Questionnaire	Levenstein et al. [98]; Fliege et al. [99]	X	X	X
Self-efficacy	SWE	Skala zur Allgemeinen Selbstwirksamkeitserwartung	Jerusalem and Schwarzer [100]	X		
Non-motor symptoms	NMSQ	Non-Motor Symptoms Questionnaire (NMSQ)	Chaudhuri et al. [101]	X	X	X
Lifestyle activities	LAQ	Lifestyle Activities Questionnaire	Carlson et al. [72], Parisi et al. [73]	X	X	X
Diet	MEDAS	Mediterranean Diet Adherence Screener	Schröder et al. [74], Hebestreit et al. [75]	X	X	X
